### 8.7.3 Sample Size & Accrual

We anticipate that about 30% of participants in the control group will come for retesting at both 3 and 6 months. With a sample size of 525 participants randomized 1:1:1 to the 3 study arms, we will have >80% power ( $\alpha=0.05$ , 2-sided) to show a difference of at least 15% in retesting rates in each of the intervention groups compared to the control group. With this sample size there will be >90% power to show a difference of at least 18% between the intervention and control groups.

## 9.0 Sustainability & Cost-Effectiveness

Repeat HIV testing among high-risk individuals is essential for the success of combination HIV prevention. By engaging men in first-time testing as part of our HIV testing incentives trial (Section 5), there may be an important opportunity for establishing healthy behaviors. To examine issues related to the sustainability of offering incentives and the cost-effectiveness of such an approach, we will quantitatively and qualitatively assess *repeat* testing behavior among participants in the study communities where we conduct the incentives trial. We will thereby address an important question that has rarely been examined: do one-time incentives strengthen or weaken individuals' likelihood of testing routinely once incentives are no longer offered? We will also address a central policy issue: the cost-effectiveness of using incentives to promote HTC and HIV treatment.

### 9.1 Longitudinal HIV Testing

In each of the study communities where the incentive trial was conducted, we will measure HTC uptake at multiple time periods after the start of the incentives trial. The time periods during which we will measure HTC uptake will range from about 12-36 months after the start of the trial so that we can monitor repeat testing period longitudinally. HTC uptake will be recorded at similar HTC venues as those used at baseline, in the incentives trial. All participants will once again receive information on when and where to find the testing venues. In these subsequent time periods, incentives offered for HTC will either be significantly smaller or non-existent, since the objective will be test the durability and sustainability of the effect of offering incentives for HTC initially. As in the incentives trial conducted at baseline, we will use electronic fingerprint biometric measurements that link participants in real-time to a study ID at the time of HIV testing to determine whether study participants HIV tested or not.

### 9.2 Cost-Effectiveness Analysis

*Intervention costs:* We will measure the full resources and associated costs of implementing the incentive interventions. Costs will include not just the incentive amounts but also costs required to deliver each intervention (home visits, staff time, prize procurement, supplies, and monitoring). Data will come from two methods: (a) Micro-costing will quantify resources used and unit costs. We will extract data from project expenditure and management records, including purchase logs and human resource records. We will record this information in structured costing spreadsheets that record each resource (e.g., counselor), category (e.g., personnel, supplies), quantity (e.g., hours), and unit costs. (b) Time and motion logs will record how staff divide time among multiple roles (within and outside the incentive intervention) to allow us to reliably apportion effort to incentive-related activities, especially when staff have other roles.

*Intervention effects:* To measure effectiveness as part of an assessment of the cost-effectiveness of incentives vs. no incentives, we will also use data from four other SEARCH Trial communities to quantify testing and virologic suppression rates for men who did not test at baseline and received no incentives for testing.

We will conduct five linked analyses. In each we will compare among incentive arms and to non-incentive SEARCH communities. (1) *Increased short-term testing:* cost per added person tested and HIV-infected person identified. (2) *Increased HIV virologic suppression:* cost per added person with virologic suppression (i.e., tested and on treatment). (3) *Reduced disease burden:* cost per averted DALY based on improved testing and treatment. This will include modeled lifetime ART health benefits and costs. (4) *Repetition of analyses 1-3 incorporating the long-term (3 year) effects of incentives* on testing (as assessed in this 3rd Aim). If the proportion of participants testing at future HTC campaigns remains similar to the proportion who tested when incentives were offered, the increased yield of testing and HIV-infected individuals identified in those future years – with **no** added incentive cost – will result in more favorable cost-effectiveness ratios. (5) *Cost implications of incentives given a community target testing level.* Increased HTC uptake at mobile venues due to incentives (and thus decreased need for resource-intensive tracking and testing) could generate overall cost *reductions* for identifying persons unaware of their infection. The main outcome metric will be how many additional high-risk men can be tested by spending fixed resources on novel rather than standard incentives.

These analyses will be conducted using customized spreadsheet-based decision tree and clinical progression simulation modeling methods adapted from our past projects [61-63]. Extensive 1-way, multi-way, threshold, and scenario sensitivity analyses will quantify the effects of input uncertainty on results. Our analytic

perspective will be the health system, for direct medical costs, discounting future costs and DALYs at 3% per year.

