##### 5.1.3.1 Inclusion Criteria

- (a) Male;
- (b) Aged  $\geq 18$  years;
- (c) Reside in one of the selected communities;
- (d) Consent to randomization to incentive strategy.

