##### 5.1.3.2 Exclusion Criteria

- (a) Migration out of study community for  $\geq 6$  months per year in the year prior to enrollment.
- (b) Intention to move away from the community.

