### 9.4 Analysis

*Long-term effects of incentives:* We will examine trends in HTC uptake over a period of up to 36 months for the individuals who participate in the incentives trial. To control for time trends in HTC uptake that may bias our results, we will also utilize longitudinal data on HTC uptake by men in the SEARCH Trial communities. We will assess whether HTC uptake is maintained at baseline levels or if instead it declines over time at rates that exceed what is observed in the SEARCH Trial among men who test at baseline.

*Cost-effectiveness:* We will conduct five linked analyses. In each we will compare among incentive arms and to non-incentive SEARCH communities. (1) Increased short-term testing: cost per added person tested and HIV-infected person identified. (2) Increased HIV treatment: cost per added person with HIV RNA suppression (i.e., tested and achieved or maintained virologic suppression). (3) Reduced disease burden: cost per averted disability-adjusted life year (DALY) based on improved testing and treatment (with higher and earlier initiation of ART). This will include modeled lifetime ART health benefits and costs. (4) Repetition of analyses 1-3 incorporating the long-term (3 year) effects of incentives on testing (as assessed in this 3rd Aim). If the proportion of participants testing at future HTC campaigns remains similar to the proportion who tested when incentives were offered, the increased yield of testing and HIV-infected individuals identified in those future years – with no added incentive cost – will result in more favorable cost-effectiveness ratios. (5) Cost implications of incentives given a community target testing level. Increased HTC uptake at mobile venues due to incentives (and thus decreased need for resource-intensive tracking and testing) could generate overall cost reductions for identifying persons unaware of their infection. The main outcome metric will be how many additional high-risk men can be tested by spending fixed resources on novel rather than standard incentives. These analyses will be conducted using customized spreadsheet-based decision tree and clinical progression simulation modeling methods adapted from our past projects. Extensive 1-way, multi-way, threshold, and scenario sensitivity analyses will quantify the effects of input uncertainty on results. Our analytic perspective will be the health system, for direct medical costs, discounting future costs and DALYs at 3% per year.

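### Section 9.2 takes its no-incentive rate from SEARCH men who did not test at baseline, but Aim 1 enrols men regardless of testing history, so the incentives-versus-none contrast is not like-for-like

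*Protocol*

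**What the plan says.** Aim 1 randomises men to lottery, loss-aversion or fixed incentives (Protocol, Sections 4 and 5.2); no arm goes without an incentive. Section 9.2 fills the gap with external data. It introduces them with "To measure effectiveness as part of an assessment of the cost-effectiveness of incentives vs. no incentives" and takes from four SEARCH communities the "testing and virologic suppression rates for men who did not test at baseline and received no incentives for testing".

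The same section then sets out five linked analyses: "In each we will compare among incentive arms and to non-incentive SEARCH communities". The first is "cost per added person tested and HIV-infected person identified". Table 1 (Section 1.1) lists cost per added person tested and linked to care, and per averted DALY, among the Aim 4 primary outcomes.

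Aim 1 eligibility (Sections 5.1.3.1 and 5.1.3.2) asks that a man be 18 or over, consent to randomisation, and "Reside in one of the selected communities". The exclusions are long absence in the past year and "Intention to move away from the community". Testing history appears in neither list. Section 3.1 adds that the study communities are candidates that were not enrolled in SEARCH.

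For the long-term effect, Section 9.4 follows the trial's participants for up to 36 months and asks whether their uptake "declines over time at rates that exceed what is observed in the SEARCH Trial among men who test at baseline".

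**The concern.** The comparator in Section 9.2 is selected on the behaviour being measured: every man who tested without an incentive at SEARCH baseline is left out. The incentive side is not selected in this way. By the protocol's own background figure, 55% of Ugandan men have never tested (Section 1.2), so an unselected sample of resident men would be expected to include many who have. If men who stayed away once are less likely to come later, the no-incentive rate is too low for the Aim 1 population. The increment is then too large and the cost per added test looks too favourable.

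Section 9.4 raises a related but distinct problem. SEARCH men chosen because they tested at baseline start at 100% uptake by definition. Aim 1 participants include those who did not come, and Section 5.7.3 plans on 30% to 50% uptake. A decline from the one starting point is not comparable with a decline from the other.

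**Working it through.** The protocol gives no figure for the incentives-versus-none effect, so there is nothing to reproduce. The check is a comparison of populations, followed by an illustration of size.

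**1. Populations.** In Section 9.2 the SEARCH side is baseline non-testers and the Aim 1 side is all enrolled men. In Section 9.4 the SEARCH side is baseline testers and the Aim 1 side is again all enrolled men. Sections 9.2 and 9.4 do not restrict the Aim 1 men, match them or standardise either side. The sensitivity analyses promised there concern uncertainty in inputs, not a difference in populations.

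**2. Inputs for the illustration.**
- p, uptake with incentives: 40% (fixed) and 50% (lottery), from Section 5.7.3.
- q, share of baseline non-testers in an unselected population: 55%, borrowed from the never-tested figure in Section 1.2; 30% as an alternative. Neither is a SEARCH figure.
- v, later no-incentive uptake in baseline non-testers: assumed 10%, range 10% to 15%.
- w, the same in other men: assumed 30%, range 20% to 40%.

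**3. Formulas.**
- No-incentive uptake in all men: u = q·v + (1 − q)·w.
- Added testing with a matched comparator: p − u. With the planned comparator: p − v.
- Overstatement of added testing: (p − v)/(p − u). With incremental cost per man held fixed, cost per added test is shown at (p − u)/(p − v) of its matched value.
- The gap between the two increments is u − v = (1 − q)(w − v), so its sign is the sign of w − v.

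**4. Main illustration.** u = 0.55 × 10% + 0.45 × 30% = 5.5% + 13.5% = 19%.
- p = 40%: 40 − 19 = 21 points matched, 40 − 10 = 30 planned; 30/21 = 1.43; cost ratio 21/30 = 0.70.
- p = 50%: 50 − 19 = 31 points matched, 50 − 10 = 40 planned; 40/31 = 1.29; cost ratio 31/40 = 0.775.

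**5. Range and reversal.**

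| Case | p | q | v | w | u | Matched | Planned | Overstatement |
|---|---|---|---|---|---|---|---|---|
| Smallest with v < w | 50% | 0.55 | 15% | 20% | 17.25% | 32.75 | 35 | 1.07 |
| Largest with v < w | 40% | 0.30 | 10% | 40% | 31% | 9 | 30 | 3.33 |
| Equal rates | 40% | 0.55 | 20% | 20% | 20% | 20 | 20 | 1.00 |
| Reversed | 40% | 0.30 | 25% | 15% | 18% | 22 | 15 | 0.68 |
| Reversed | 50% | 0.55 | 25% | 15% | 20.5% | 29.5 | 25 | 0.85 |

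The 3.33 needs 31% uptake without incentives across all men. That already exceeds the lower planning rate with fixed incentives (30%, Section 5.7.3), so it marks an extreme.

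**The case against.** Several points on the other side stand.

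- **No contradiction between 9.2 and 9.4.** A reader might infer one because they pick opposite SEARCH subsets. They answer different questions: what testing would have been without an incentive, and whether testing that has occurred is sustained. Section 9.4 also first refers to SEARCH men without restriction, and Section 9.3 interviews men who tested initially, so a tester-to-tester comparison may be intended. The text does not say so.
- **The five analyses are not wholly affected.** Each also compares the incentive arms with one another, and that part is randomised. The main metric named with the fifth analysis, novel against standard incentives, is of this kind.
- **Direction is not proven.** It depends on v being below w. That is likely, but the documents give neither rate.
- **Large multiples are not supported.** A reader might assume 15% to 25% in non-testers and 30% to 40% in all men, and at 50% uptake obtain 25/20 = 1.25-fold to 35/10 = 3.5-fold. But 30% and 40% are the planning rates with fixed incentives in Section 5.7.3. Using them as no-incentive rates amounts to assuming that fixed incentives add nothing.
- **The choice may be deliberate.** Sections 1.1 and 9.0 frame Aim 1 around men unaware of infection and first-time testing, which would suit a comparator of non-testers. The eligibility criteria do not impose that limit.

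It can also be said that standardisation belongs in an analysis plan, which is not shown. That is fair for the method of adjustment. It does not cover the comparator population, which the protocol itself fixes.

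**Conclusion.** The mismatch is in the text and holds whatever the rates turn out to be: Section 9.2 sets an Aim 1 population unselected on testing against SEARCH men selected for not testing. The likely consequence is overstated added testing and understated cost per added test. The illustration gives about 1.3- to 1.4-fold at 40% to 50% incentive uptake. This rests on assumed values of v and w and a borrowed q; the sign turns on v being below w. The effect on cost per HIV-infected man identified or per averted DALY was not computed, since it also depends on undiagnosed prevalence in each group.

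Section 9.4 has its own like-for-like fault, which is not sized here.

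Only the SEARCH contrast is affected. The primary outcomes of Aims 1 to 3, the sample sizes and the randomised comparisons among incentive arms are untouched. This should be fixed because it feeds a listed Aim 4 primary outcome, but it does not threaten the trial's main results.

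**What to change.** In Section 9.2, define the no-incentive comparator as all SEARCH men who meet the Aim 1 eligibility criteria. Count testing at venue types and over a window as similar to Aim 1 as the data allow, and standardise to the Aim 1 men on baseline characteristics recorded in both studies. Alternatively, restrict both sides to the same prior-testing status, if both studies recorded it; the protocol does not list the contents of the Aim 1 baseline questionnaire, so this needs checking.

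In Section 9.4, compare Aim 1 baseline testers with SEARCH baseline testers, or all men with all men, and say which.

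In both sections, label the SEARCH contrast as non-randomised and report it apart from the randomised comparisons among arms.

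The cost is revised wording and a different extract of SEARCH data, subject to what SEARCH recorded on venue and timing. The cost-effectiveness ratios will probably be less favourable.

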### 3. Study Site & Population

#### 3.1 Community Selection

We will conduct study activities in rural Uganda, enrolling adults ( $\geq 18$  year old) from up to four communities of 10,000 persons each in southwestern and/or eastern Uganda. The study communities will be selected from the Ugandan candidate communities that met the initial trial eligibility for the ongoing Sustainable East Africa Research in Community Health (SEARCH) HIV test and treat Trial (NCT: 01864603; Co-PIs [name] and [name] are Investigators in the SEARCH Trial), *but were not enrolled in the SEARCH trial*. The SEARCH Trial consists of 32 communities selected from 52 candidate communities that met the initial trial eligibility criteria of a rural geopolitical community, with population 10,000, within the catchment area of a PEPFAR-supported HIV clinic in southwestern Uganda, eastern Uganda or western Kenya; 20 candidate communities were not enrolled in SEARCH. All candidate study communities are largely agrarian ( $>70\%$  of adults in commercial or subsistence farming), with pre-existing ART clinics and free facility-based HIV testing services available locally. Working with the SEARCH Trial team, we have already performed ethnographic mapping, and reviewed national census and epidemiologic data for each candidate community, and have established relationships with the Ministry of Health District Health Officer within each community, facilitating our engagement with these well-characterized communities for the Incentives Trial.

In our Aim 3 trial of retesting for HIV among high-risk HIV-uninfected adults, we will conduct study activities in southwestern Uganda in the urban and peri-urban areas in and around Ibanda and Mbarara Districts, as well as the study communities in which Aims 1-2 were implemented. The urban areas in and around Ibanda and Mbarara Districts include multiple venues at which adults congregate for alcohol consumption and are frequented by groups considered at-risk for HIV infection, including commercial sex workers and long-distance truck drivers.

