### 5.7.3 Sample Size & Accrual

The trial will have about 3,000 total participants. About 1,000 participants will be randomized to each type of incentive strategy (fixed incentives, lottery-based incentives, loss aversion incentives). There will also be equal numbers of participants assigned to each of the incentive amounts that are chosen. The sample size has been chosen to ensure there is adequate power for the primary *and* secondary analyses. For the primary analyses, if we assume HTC uptake is as low as 30% with fixed incentives, the study will have >80% power to detect a difference ( $\alpha=0.05$ , two-sided) in HTC uptake as small as 6% between the novel incentive and fixed incentive groups. If HTC uptake is 40% with fixed incentives, the study will have >80% power to detect a difference in HTC uptake as small as 7% in each of the novel incentive arms. For secondary analyses, if we assume 40% HTC uptake with fixed incentives (N=400), and 50% with lottery (N=500), we will have >80% power to detect a difference of at least 6% in HIV prevalence between testers in novel and fixed incentive groups (assuming prevalence of 6% in the fixed incentive group).

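### The cost-effectiveness sections name only deterministic-type sensitivity analyses; no named method carries sampling error or between-community variation into the results

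*Protocol*

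**What the plan says.** Section 9.2 sets out five linked cost-effectiveness analyses. Their outcomes include "cost per added person tested and HIV-infected person identified", cost per added person with virologic suppression, and cost per DALY averted. On comparators it says: "In each we will compare among incentive arms and to non-incentive SEARCH communities". Aim 1 has no arm without incentives, so for testing the contrast of incentives with none rests on outside data: "we will also use data from four other SEARCH Trial communities to quantify testing and virologic suppression rates for men". These comparator men are limited to baseline non-testers, and they were offered no incentive. The trial itself recruits "from up to four communities of 10,000 persons each" (section 3.1).

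The modelling uses "customized spreadsheet-based decision tree and clinical progression simulation modeling methods adapted from our past projects". Uncertainty is covered by one sentence, "Extensive 1-way, multi-way, threshold, and scenario sensitivity analyses will quantify the effects of input uncertainty on results", which section 9.4 repeats unchanged. Neither section mentions a probabilistic analysis, resampling, an interval for a ratio, net benefit or clustering by community.

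**The concern.** Cost per added tester, per added HIV-positive man and per added suppressed person each divide by a difference estimated from a sample. Moving inputs over chosen ranges shows how the model responds. It attaches no probability to those ranges, so it yields neither a confidence nor a credible interval. A ratio also becomes unstable when its denominator could plausibly be zero.

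The SEARCH contrast adds a second source of error. Up to four communities with incentives are set against four without, so exposure is confounded with community, and variation between communities belongs in the uncertainty.

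At stake is the ranking of incentive types, or of incentives against none, on ratios that the data may not be able to tell apart.

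**Working it through.** **Inputs.** From section 5.7.3: "About 1,000 participants will be randomized to each type of incentive strategy"; uptake 30% with fixed incentives; detectable difference 6 points; two-sided alpha 0.05; 6% prevalence among testers in the fixed group; and, for the secondary analysis, 40% versus 50% uptake. From section 6.6.3: 50% suppression in controls, a 15-point difference, about 400 adults (200 per arm). The documents give no ICC, no number of SEARCH men and no split of incremental cost into fixed and per-tester parts. Values used for these below are assumptions.

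**1. The plan's own figure.** Power for 30% versus 36% with 1,000 per arm, pooled-variance normal approximation: (0.06 − 1.96 × √(2 × 0.33 × 0.67/1000)) / √((0.30 × 0.70 + 0.36 × 0.64)/1000) = (0.06 − 0.0412)/0.0210 = 0.895, which gives 81.5%. The stated figure of more than 80% reproduces.

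**2. Added testers at that effect.** Per 1,000 men per arm: 360 − 300 = 60. SE = √(1000 × (0.30 × 0.70 + 0.36 × 0.64)) = 21.0. The 95% CI is 60 ± 41, or 19 to 101.

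**3. What this does to cost per added tester.** Let f be the share of incremental cost that is fixed when 60 men are added. Relative to its value at 60, the ratio at D added men is (1 − f) + f × 60/D. Unrounded limits are 18.9 and 101.1.

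| f (assumed) | at D = 18.9 | at D = 101.1 | fold range |
|---|---|---|---|
| 0% | 1.00 | 1.00 | 1.0 |
| 25% | 1.54 | 0.90 | 1.7 |
| 50% | 2.09 | 0.80 | 2.6 |
| 100% | 3.17 | 0.59 | 5.4 |

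**4. Added HIV-positive men found.** With 6% positivity in both arms: 300 × 0.06 = 18 and 360 × 0.06 = 21.6, difference 3.6. SE = √(1000 × (0.018 × 0.982 + 0.0216 × 0.9784)) = 6.23. The CI is −8.6 to 15.8, which includes zero. At 40% versus 50% uptake and 6% in both arms, the difference is 0.6 points (−0.8 to 2.0). With 6% versus 12% positivity the picture changes: 43.2 − 18 = 25.2 (CI 10.1 to 40.3) at 30%/36% uptake, and 60 − 24 = 36 (18.5 to 53.5) at 40%/50%.

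**5. Aim 2, 50% versus 65%, 200 per arm.** SE = √((0.50 × 0.50 + 0.65 × 0.35)/200) = 0.0489; difference 15 points (5.4 to 24.6). Inverted, this is 6.7 persons offered per added suppression (4.1 to 18.4).

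**6. SEARCH contrast.** Assume four communities per side, 750 men each (3,000/4, borrowed from the trial), uptake near 35% and ICC 0.005 to 0.05. The design effect 1 + 749 × ICC is 4.7 to 38.5. SE = √(design effect × 2 × 0.35 × 0.65/3000) = 2.7 to 7.6 points, against 1.2 if men were independent.

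For an assumed 30% versus 40%, with a t critical value of 2.447 on 6 df:

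| Men per community (assumed) | Ignoring clustering | ICC 0.01 | ICC 0.02 |
|---|---|---|---|
| 250 | 5.8 to 14.2 points | 0.3 to 19.7 | −2.7 to 22.7 |
| 750 | 7.6 to 12.4 points | 1.3 to 18.7 | −2.0 to 22.0 |

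**The case against.** The uncertainty sentence is not exclusive. A reader might infer that the plan rules out other methods, or that the ratios will carry no valid interval. The text says neither. Multi-way analysis does not strictly exclude joint simulation, trial differences could be varied over their own intervals, and an SAP or economic plan not shown here may add methods. All of that stands. What remains is that the protocol assigns the quantifying of input uncertainty to a named list, twice, and nothing on that list carries sampling or between-community error.

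A reader might also take the 5.4-fold range as the effect of sampling alone. That holds incremental cost fixed. Sections 5.3 to 5.5 pay incentives only on testing, and section 5.2 equalises expected value across strategies within a tier, so part of the cost moves with added testers and the range can shrink to 1.0-fold.

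Nor is the ratio for HIV-positive men always unbounded. Section 5.7.2 hypothesises higher positivity with lottery, and at 6% versus 12% the denominator stays clear of zero.

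Three further points stand. The SEARCH magnitudes follow from the assumed ICC and community size, and the comparator is restricted to men who did not test at baseline, so 750 may be too many. Resampling four communities per side would not give a reliable interval, and no interval removes non-randomised bias. Cost per DALY includes modelled lifetime effects, so it is not simply a cost divided by a trial difference, and the fifth analysis uses a metric that stays defined when arms do not differ.

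**Conclusion.** The point holds as a gap in the named methods. At the protocol's own design values the denominator for added testers has a 95% CI of 19 to 101 around 60. The consequence for cost per added tester lies between 1.0-fold and 5.4-fold, and the documents do not give the cost split that would place it. An unbounded ratio for HIV-positive men depends on equal 6% positivity in both arms. For the SEARCH contrast, an assumed ICC of 0.01 to 0.02 widens the interval enough to reach or nearly reach zero for an assumed 10-point difference. This is a worthwhile, low-cost improvement to the secondary Aim 4. It does not touch the primary analyses of Aims 1 to 3.

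**What to change.** In sections 9.2 and 9.4:

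- **Randomised arms.** Bootstrap participants within arms, recompute incremental cost and effect jointly in each replicate, and report incremental net benefit with acceptability curves. This keeps the dependence of incentive cost on testing and remains defined when the effect difference is near zero.
- **SEARCH contrast.** Analyse at community level with t-based intervals suited to few clusters, show results over a stated ICC range, and label it a non-randomised comparison whose bias no interval removes.
- **External model parameters.** Keep the one-way, multi-way, threshold and scenario analyses for these.

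The cost is analyst time, with no new data collection. The downside is wider and less favourable intervals.
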